## Methods

### Study Site and Design

The TREND study is a hospital-based, prospective observational study of children with clinical CAP and asymptomatic controls. The study will take place at Sachs’ Children and Youth Hospital, Stockholm, which has one of the largest pediatric emergency departments in Sweden with over 30,000 visits each year. The study is planned to be conducted from November 2017 to December 2019. The study is registered at clinicaltrials.gov (ID: NCT03233516) July 28, 2017.

### Study Participants

#### Case Definition

Children aged 1 to 59 months with clinical CAP (both severe and nonsevere) according to the World Health Organization (WHO) criteria are enrolled as cases (Figure 1). The inclusion criteria (all inclusion criteria to be met to be eligible for participation in the study) are as follows: age 1 to 59 months, reported or observed breathing troubles/coughing, observed age-adjusted tachypnea (≥50 breaths/min in children aged 1-12 months, ≥40/min in children aged >1 year) or chest indrawing, and written informed consent. The exclusion criteria are as follows: previously included as a case in the study or hospitalized during the previous 14 days. Inhalation with a rapid-acting bronchodilator (≥1 dose in children aged <2 years and ≥3 doses in children aged 2-4 years) will be administered to children with wheezing and chest indrawing to improve the specificity of the WHO clinical CAP criteria, as suggested by the PERCH study team [43]. Resolved chest indrawing after bronchodilator challenge will be recorded but not considered as an exclusion criterion to be able to exclude these patients in a subanalysis as well as to analyze these patients separately.

**Figure 1 figure1:**
[figure not shown]
Algorithm for screening and enrollment of study subjects in the Trial of Respiratory infections in children for ENhanced Diagnostics (TREND) study.

#### Control Definition

Children aged 1 to 59 months treated for a minor orthopedic (elective, eg, hand surgery, or acute) or minor surgical disease, for example, minor trauma (excluding appendicitis, major burns, major trauma, etc) are enrolled as controls. No formal matching will be performed, but age and season will be considered in the analyses. The exclusion criteria are symptoms of respiratory disease 7 days before enrollment, previous inclusion as a control in the study, or hospitalized during the previous 14 days. The guardians of the controls will be contacted by email/telephone 1 to 2 weeks after enrollment to collect information regarding the potential respiratory symptoms developed after discharge. Cases and controls will be included in the emergency unit, and additional controls will also be included in the hand surgery unit of the hospital.

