**Methods:**

Children aged 1 to 59 months with clinical CAP as well as healthy, hospital-based, asymptomatic controls will be included at a pediatric emergency hospital in Stockholm, Sweden. Blood (analyzed for MxA and C-reactive protein) and nasopharyngeal samples (analyzed with real-time polymerase chain reaction as the gold standard and antigen-based mariPOC respi test as well as saved for future analyses of a novel recombinase polymerase amplification–based point-of-care test for respiratory pathogens) will be collected. A newly developed algorithm for the classification of CAP etiology will be used as the reference standard.

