Myxovirus resistance protein A (MxA) is an intracellular protein that is upregulated upon activation of the antiviral defense system. Increased blood MxA has been reported to be specific for viral infection [13-15]. There is a commercially available rapid diagnostic test, FebriDx, that qualitatively detects MxA and CRP at cutoffs of 40 ng/ml and 20 mg/ml, respectively. The test has been reported to have 85% (29/34) sensitivity and 93.4% (183/196) specificity to rule out a bacterial infection in patients (adults and children) with febrile respiratory infection [16]. However, no studies have focused on MxA in children with CAP. It was previously shown that virus-positive asymptomatic children had lower MxA levels as compared with virus-positive symptomatic children with respiratory symptoms [14]. As current viral real-time polymerase chain reaction (PCR) testing of upper respiratory specimens (ie, the routine method for diagnosing respiratory tract infections) is complicated by frequent asymptomatic detection, MxA has the potential to facilitate the interpretation of viral PCR positivity in terms of clinical relevance in children with CAP [17].

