### Study Variables

Information regarding the study subjects (initials, year and month of birth, sex, date of inclusion, and postal code), number of siblings, days of illness, current symptoms (fever, coughing, runny nose, wheezing, whooping, shortness of breath, hoarseness, sore throat, ear secretion, inability to feed, lethargy, vomiting, and diarrhea), vaccinations, antibiotic treatment, medication, underlying diseases, heredity for asthma, previous hospitalization, recent (last 3 months) trips abroad (if yes, where and for how long), allergies, smoking in the family, recent contact with unwell individuals, breastfeeding, preschool, origin of parents, and socioeconomic status will be collected through a standardized questionnaire based on previous studies [46,47].

Clinical parameters (respiratory rate, consciousness according to the AVPU scale—alert, verbal stimuli, pain stimuli, unresponsive—pulse, peripheral oxygen saturation, weight, body temperature, vomiting, head nodding, central cyanosis, stridor, chest indrawing, nasal flaring, grunting, pedal edema, skin turgor, capillary refill, cool peripheries, and pulmonary auscultatory findings—decreased breath sounds, crackles/crepitations, bronchial breath sounds, and wheezing) and antipyretic medication prescribed within less than 4 hours will be registered by the study doctor responsible for patient screening/enrollment. To avoid overloading the case report form, information about symptoms and danger signs that are rare in a Swedish context (eg, jaundice, bulging fontanelle, rash, gallop rhythm, weak peripheral pulses, and tender liver mass) will be retrospectively collected from the medical records if deemed necessary. Some clinical parameters are routinely recorded multiple times at the emergency unit. In these cases, the most extreme value (highest pulse/respiratory rate/body temperature and lowest peripheral oxygen saturation) during the visit at the emergency unit enrollment will be recorded. Information regarding admission; length of hospital stay; routine clinical examination; radiological, microbiological, and biochemical analyses (eg, bacterial cultures and blood gas tests); treatment; discharge diagnosis; and complications (parapneumonic effusion and sepsis) will be retrospectively collected from the medical records.

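### Controls are screened only for respiratory symptoms, so a child with a non-respiratory viral illness is eligible and would modestly bias the MxA comparison of viral CAP with controls toward no difference

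*Protocol article*

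**What the plan says.** The Control Definition section takes as controls: "Children aged 1 to 59 months treated for a minor orthopedic (elective, eg, hand surgery, or acute) or minor surgical disease". It then lists the exclusions: "The exclusion criteria are symptoms of respiratory disease 7 days before enrollment, previous inclusion as a control in the study, or hospitalized during the previous" (the window for hospitalization is 14 days). No other exclusion for controls appears in the text. The contact with guardians 1 to 2 weeks later serves to "collect information regarding the potential respiratory symptoms developed after discharge", so it too is limited to the airway. For the control analyses, that section names only age and season.

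The Methods paragraph of the abstract describes the same group as "healthy, hospital-based, asymptomatic controls".

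The Introduction (Biomarkers in Pediatric Respiratory Tract Infections) calls MxA "an intracellular protein that is upregulated upon activation of the antiviral defense system" and adds: "Increased blood MxA has been reported to be specific for viral infection". Neither statement is confined to respiratory infection.

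The questionnaire in Study Variables asks study subjects about current symptoms. Fever is on the list, which continues with "inability to feed, lethargy, vomiting, and diarrhea), vaccinations, antibiotic treatment, medication, underlying diseases".

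**The concern.** The exclusion rule is narrower than both the description of the controls and the biology of the marker. A respiratory-only screen suits a case-control study of respiratory etiology. It fits less well where controls supply the reference level of a marker that responds to viral infection anywhere in the body.

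Other planned data would not reliably identify an affected control. The PCR panel is made up of respiratory agents, so an illness caused by a virus outside the panel goes undetected. CRP is not routinely measured in controls (Ethics Approval and Consent to Participate). If the virus is on the panel (adenovirus and enterovirus are), the child joins the virus-positive controls. That group is the reason for raising the control target from 42 to 120, and it serves the aim of using MxA to interpret PCR positivity.

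At stake is one of the two comparisons on which the study is sized. High MxA in unwell controls raises the control mean and spread, and counts against the specificity of MxA.

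**Working it through.** **Inputs from Study Size and Power Calculation.** Difference 500 µg/l; SD 1000 in viral CAP and 300 in bacterial CAP or controls; two-sided alpha 0.05; power 80%; 20% added; 300 cases and 120 controls; 45% of cases viral and 14% bacterial; 35.4% of asymptomatic children virus-positive.

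**The plan's own figure.** n per group = (1000² + 300²) × (1.960 + 0.842)² / 500² = 34.2, rounded up to 35. Then 35 × 1.2 = 42, as stated. Also 42 / 0.14 = 300 cases and 42 / 0.354 = 118.6, stated as 120 controls. Expected viral CAP cases: 300 × 0.45 = 135. Expected virus-positive controls: 120 × 0.354 = about 42. The gap in the control definition does not alter these figures.

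**Assumption.** The share p of controls with a current non-respiratory viral illness is not in the documents. I take 2-10%, which is about 2 to 12 of 120 children, and let their MxA lie 500 µg/l above that of other controls, the only difference the article supplies.

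- Rise in control mean: 500p.
- Remaining difference: 500(1 − p).
- Control SD, version A (affected controls keep SD 300): √(300² + p(1 − p) × 500²).
- Control SD, version B (affected controls have the viral CAP SD of 1000): √((1 − p) × 300² + p × 1000² + p(1 − p) × 500²).
- Power, by normal approximation under version B, with 135 viral cases and 120 controls.

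| p | Rise in control mean | Difference | SD, A | SD, B | Power, 135 v 120 |
|---|---|---|---|---|---|
| 0 | 0 | 500 | 300 | 300 | 99.98% |
| 2% | 10 | 490 | 308 | 336 | 99.97% |
| 5% | 25 | 475 | 319 | 384 | 99.92% |
| 10% | 50 | 450 | 335 | 451 | 99.71% |

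Worked line for p = 10%: version A is √(90,000 + 22,500) = 335; version B is √(81,000 + 100,000 + 22,500) = 451. The standard error under B is √(1,000,000/135 + 203,500/120) = 95.4, so 450/95.4 − 1.96 = 2.76, which is a power of 99.7%.

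Even at p = 20%, power with 135 and 120 is about 98%. With 135 viral cases and 42 virus-positive controls it is 98.2% at p = 10%. Only at the minimum of 42 per group does it fall visibly, from 87% at p = 0 to 76% at p = 10%.

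**Specificity.** Let S be the share of unaffected controls below a cutoff, and Se the share of affected controls above it. Apparent specificity falls by pS − p(1 − Se) = p(S + Se − 1), which is at most p. The ceiling is therefore 2-10 percentage points, reached only if every affected control is above the cutoff and every other control below it.

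**Virus-positive controls.** One misplaced child among about 42 is 1/42 = 2.4% of that group.

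**The case against.** The case for leaving the plan alone has four parts.

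- **The number affected may be small.** Controls have minor orthopedic or surgical conditions, and some come for elective surgery. This stands: the size is an assumption, and the low end may be nearer the truth.
- **The gap may be closed elsewhere.** The screening algorithm (Figure 1) is not shown, and the article condenses a fuller protocol. That is possible. But the text gives the exclusions as a complete list, and nothing in it points to a further criterion.
- **Means and SDs overstate the effect of a few outliers.** The sample size allows for nonparametric testing, and the methods are to follow the distribution of the data. This stands as to size, not direction.
- **Excluding unwell controls is a preference.** It makes controls healthier and can flatter specificity. This is a fair caution, but the article already describes its controls as healthy and asymptomatic, so the exclusion brings the group into line with that description. Showing both results answers the rest.

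A reader might infer more than the documents support:

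- One might say that such children are counted as virus-free controls. No such group is defined. The comparisons are with all controls and with virus-positive controls, and about 35% of controls are expected to be virus-positive.
- One might add recent live vaccination as a source of raised MxA. Nothing in the article links vaccination to MxA, and it does not say that vaccination dates are recorded.
- One might assume a shift of 1000 µg/l. That is twice the difference the article uses for viral CAP itself.

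**Conclusion.** The point holds in a limited form. As written, the control rule admits children with a current non-respiratory viral illness, which conflicts with the description of the controls and with what MxA is said to measure. The bias in the comparison of viral CAP with controls runs toward no difference. On an assumed 2-10% of affected controls with MxA 500 µg/l higher, it is 10-50 µg/l, or 2-10% of the 500 µg/l difference. The control SD rises from 300 to about 308-335, or to about 336-451 if affected children share the viral CAP SD. Both the share and the shift are assumptions.

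It would be tempting to conclude that the study loses power or that its main question is compromised. Neither follows. Power at the planned numbers is essentially unchanged, and the comparison of viral with bacterial CAP does not involve controls. The harm is a modestly biased estimate and a lower apparent specificity against controls. It deserves correction because the correction is cheap.

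**What to change.** In Control Definition, add current fever, vomiting or diarrhea to the exclusion criteria for controls.

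Enrollment began in November 2017, so a rule is also needed for controls already included. Use the current-symptom items in the questionnaire to leave children with fever, vomiting or diarrhea out of the main MxA comparison, both for all controls and for virus-positive controls. Show the result with every enrolled control as a sensitivity analysis. Set the rule before MxA results are linked to study group, so that it cannot look like an explanation found afterwards for high control values.

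Keep to these three current symptoms. The questionnaire items are described as current, with no 7-day look-back stated, and rash is not on the case report form: it is taken from medical records only if deemed necessary.

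Cost: one line in the eligibility criteria, made during recruitment, and one line in the analysis, with no new data. A few controls are lost from the main comparison, some of whose symptoms will not be viral, and the control group becomes slightly healthier than the children who attend.

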### Biological Samples

Capillary blood samples and nasopharyngeal aspirates and swabs will be collected from all study subjects. For the MxA analysis, 20 µl of blood will be collected using a heparinized plastic end-to-end capillary and then immediately diluted in a prefilled tube containing an in-house buffer [14]. The nasopharyngeal swabs for the mariPOC respi analyses will be diluted in 1.3 ml of a commercial buffer, as advised by the manufacturer ArcDia International Oy Ltd. The nasopharyngeal aspirates for the PCR analyses will be collected in a standardized manner, as has previously been published, but mixed with 1.3 ml of saline to mirror the protocol for the mariPOC respi [17]. All samples will be taken within 24 hours from arrival at the emergency unit, and the time of blood and nasopharynx sampling will be recorded. It will also be noted if antibiotics have been given before sampling. Samples that are not analyzed at the point of care will be stored at −80°C and shipped on dry ice to minimize degradation of the analytes of interest. All samples collected in the study will be stored according to the Swedish act: Biobanks in Medical Care (SFS 2002:297).

### Microbiological and Biochemical Analyses

Real-time PCR analysis based on the TaqMan technique will be performed in batches on the nasopharyngeal aspirates at Sahlgrenska University Laboratory, Gothenburg, using previously described methods [44]. The PCR detects the following respiratory agents: influenza A/B, RSV A/B, adenovirus, bocavirus, coronavirus (HKU1, NL63, OC43, and 229E), hMPV, PIV 1-3, rhinovirus, enterovirus, *S pneumoniae*, *H influenzae,*
* B pertussis*, and *Mycoplasma pneumoniae*.

mariPOC respi will be performed on the nasopharyngeal swabs directly at the emergency room at Sachs’ Children and Youth Hospital at the time of enrollment [32]. The test detects the following respiratory agents: influenza A/B, RSV, adenovirus, bocavirus, coronavirus, hMPV, PIV 1-3, and *S pneumoniae.*

Analyses of MxA will be performed in batches at the Institute of Biomedicine, University of Turku, Finland, using an in-house enzyme immunoassay, as previously described [14].

CRP will be analyzed using the Alere Afinion AS100 Analyzer commercial point-of-care kit at the emergency room at Sachs’ Children and Youth Hospital. If multiple CRP tests are performed, the highest value less than 48 hours from arrival at the emergency unit will be recorded [45]. A small amount of blood will be stored to allow future analysis of, for example, PCT if deemed necessary.

### Study Variables

Information regarding the study subjects (initials, year and month of birth, sex, date of inclusion, and postal code), number of siblings, days of illness, current symptoms (fever, coughing, runny nose, wheezing, whooping, shortness of breath, hoarseness, sore throat, ear secretion, inability to feed, lethargy, vomiting, and diarrhea), vaccinations, antibiotic treatment, medication, underlying diseases, heredity for asthma, previous hospitalization, recent (last 3 months) trips abroad (if yes, where and for how long), allergies, smoking in the family, recent contact with unwell individuals, breastfeeding, preschool, origin of parents, and socioeconomic status will be collected through a standardized questionnaire based on previous studies [46,47].

Clinical parameters (respiratory rate, consciousness according to the AVPU scale—alert, verbal stimuli, pain stimuli, unresponsive—pulse, peripheral oxygen saturation, weight, body temperature, vomiting, head nodding, central cyanosis, stridor, chest indrawing, nasal flaring, grunting, pedal edema, skin turgor, capillary refill, cool peripheries, and pulmonary auscultatory findings—decreased breath sounds, crackles/crepitations, bronchial breath sounds, and wheezing) and antipyretic medication prescribed within less than 4 hours will be registered by the study doctor responsible for patient screening/enrollment. To avoid overloading the case report form, information about symptoms and danger signs that are rare in a Swedish context (eg, jaundice, bulging fontanelle, rash, gallop rhythm, weak peripheral pulses, and tender liver mass) will be retrospectively collected from the medical records if deemed necessary. Some clinical parameters are routinely recorded multiple times at the emergency unit. In these cases, the most extreme value (highest pulse/respiratory rate/body temperature and lowest peripheral oxygen saturation) during the visit at the emergency unit enrollment will be recorded. Information regarding admission; length of hospital stay; routine clinical examination; radiological, microbiological, and biochemical analyses (eg, bacterial cultures and blood gas tests); treatment; discharge diagnosis; and complications (parapneumonic effusion and sepsis) will be retrospectively collected from the medical records.

Personal identification numbers of all the study subjects will be linked to the national health and population registers to collect information regarding deaths, previous immunization, and discharge diagnoses according to the International Statistical Classification of Diseases and Related Health Problems 10 (ICD-10) as well as Anatomic Therapeutic Chemical classification system codes for prescribed drugs.

### Classification of Etiology in the Trial of Respiratory Infections in Children for Enhanced Diagnostics Study

The algorithm for classifying etiology in the TREND study is based on the current literature and will classify children into viral, bacterial, atypical bacterial, mixed viral-bacterial, and undetermined infections based on clinical, microbiological, radiographic, and biochemical findings (Figure 2). A second, stricter algorithm only considering microbiologically confirmed diagnoses will be used in a complementary subanalysis (Figure 3).

**Figure 2 figure2:**
[figure not shown]
Classification of community-acquired pneumonia etiology in the Trial of Respiratory infections in children for ENhanced Diagnostics (TREND) study. CAP: community-acquired pneumonia; CRP: C-reactive protein; hMPV: human metapneumovirus; PCR: polymerase chain reaction; PIV: parainfluenza virus; RSV: respiratory syncytial virus.

**Figure 3 figure3:**
[figure not shown]
Classification of community-acquired pneumonia (CAP) etiology in the Trial of Respiratory infections in children for ENhanced Diagnostics study—strict definition. CRP: C-reactive protein; hMPV: human metapneumovirus; PCR: polymerase chain reaction; PIV: parainfluenza virus; RSV: respiratory syncytial virus.

### Long-Term Complications

Long-term complications (asthma and number of hospital-requiring respiratory infections) will be assessed by linking to the National Patient Register. Asthma will be classified according to the ICD-10 diagnosis and/or prescriptions of asthma medication in the Swedish Prescribed Drug Register using a previously validated algorithm [48].

### Study Size and Power Calculation

A total of 300 cases and 120 controls are estimated to be included in the TREND study. For the sample size calculation, we focused on the assessment of MxA levels in cases with viral CAP as compared with cases with bacterial CAP/controls (study I). Overall, 2 power calculations were made, 1 for viral CAP versus bacterial CAP and 1 for viral CAP versus controls. The following assumptions were made: (1) A difference in MxA level of 500 µg/l between the groups was considered clinically relevant. (2) A standard deviation of 1000 and 300 was assumed in cases with viral CAP and bacterial CAP/controls, respectively, based on previous studies on MxA [13,14]. Using an alpha level of .05 (2 sided) at an 80% power, with an additional 20% to account for nonparametric testing and multivariate analyses, 42 children in each group (viral CAP, bacterial CAP, and controls) would be needed. To ensure that enough of the included cases would fulfill the study definitions for viral and bacterial CAP, the proportion of children with viral and bacterial CAP (TREND definition) was calculated in our previous study that assessed Swedish children with x-ray–verified CAP [47]. By doing this, the prevalence of viral and bacterial CAP was estimated at 45% and 14%, respectively. Hence, 300 cases and 42 controls would be needed to ensure sufficient collection of cases with viral and bacterial CAP, respectively. We also would like to compare viral CAP cases with controls testing positive for 1 or more viruses by PCR. In our previous study, 35.4% of asymptomatic children tested positive for 1 or more viruses. Hence, to include a sufficient number of virus-positive controls, we aim at including 300 cases and 120 controls in the TREND study.

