
### Difficulties in Pediatric Community-Acquired Pneumonia Etiology Studies

The WHO criteria for clinical CAP lack specificity and will result in the inclusion of a significant proportion of children who will not have true CAP, including children with bronchiolitis and asthma [57]. To improve the specificity of the WHO criteria for clinical CAP, a rapid-acting bronchodilator will be administered to children with wheezing and chest indrawing, as suggested by the PERCH study team [43]. Other clinical parameters from the PERCH study will also be included and used for further subanalyses [43].

Conducting research in the pediatric emergency department is difficult [58]. High patient flows and long waiting times create a stressful environment for all personnel categories. Motivating nurses/doctors to spend the extra time and effort it takes to recruit patients is, therefore, challenging. Continuous education/information about the research project, interpersonnel teamwork (nurse and doctor), and incentives are all key success factors. Recruitment of healthy controls in this age group is an obvious challenge as the sampling (blood and nasopharyngeal sampling) causes discomfort to the child. Therefore, attempts have been made to include patients who will undergo elective hand surgery (and thereby be sedated during the sampling). Certain clinical parameters can be deceptive if not recorded correctly, which is a potential source of bias. In children where peripheral oxygen saturation and heart rate are measured continuously, data will still only be recorded at certain time points when the children are at rest.

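### The 300 cases rest on a 14% bacterial share from x-ray-verified CAP, applied without margin to WHO clinical CAP, so 42 bacterial cases are not secured

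*Protocol article*

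**What the plan says.** Under Study Size and Power Calculation the article sizes the study for a difference in MxA level between viral CAP and bacterial CAP, and between viral CAP and controls. The inputs are: "A difference in MxA level of 500 µg/l between the groups was considered clinically relevant"; "A standard deviation of 1000 and 300 was assumed in cases with viral CAP and bacterial CAP/controls, respectively"; "Using an alpha level of .05 (2 sided) at an 80% power"; and an allowance, "with an additional 20% to account for nonparametric testing and multivariate analyses". The result is 42 children in each group.

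To turn 42 per group into a number of cases, the share of viral and bacterial CAP (by the TREND definition) "was calculated in our previous study that assessed Swedish children with x-ray–verified CAP". This gave 45% viral and 14% bacterial. The article then concludes: "Hence, 300 cases and 42 controls would be needed to ensure sufficient collection of cases with viral and bacterial CAP, respectively". For controls, 35.4% of asymptomatic children in the earlier study were virus-positive, and so, "to include a sufficient number of virus-positive controls, we aim at including 300 cases and 120 controls in the TREND study".

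The Case Definition section enrols on age, cough or breathing trouble, and tachypnea or chest indrawing, severe and nonsevere alike. No radiographic criterion is listed, and children whose indrawing resolves after a bronchodilator stay in. Radiology is taken retrospectively from medical records (Study Variables). The section on difficulties in etiology studies says that the WHO criteria "lack specificity and will result in the inclusion of a significant proportion of children who will not have true CAP", and names bronchiolitis and asthma.

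**The concern.** The 14% describes a more selected population than the one enrolled. The article itself says that the enrolled population is diluted with children who do not have pneumonia, yet the sample-size section does not adjust the 14%, adds no margin, and sets no rule tying the end of enrolment to the bacterial count.

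The first specific objective is the diagnostic accuracy of MxA for viral CAP, and the bacterial cases are the main group in which specificity against viral CAP is estimated. If far fewer than 42 arrive, that estimate is less precise than a reader of the sample-size paragraph would expect. The complementary analysis under the strict algorithm, which counts only microbiologically confirmed diagnoses, would probably have fewer still.

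**Working it through.** **1. Reproducing the plan's figures.** Inputs from Study Size and Power Calculation: difference 500, SDs 1000 and 300, two-sided alpha 0.05, power 80%, plus 20%.

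- n per group = (1.96 + 0.842)² × (1000² + 300²) / 500² = 34.2, rounded up to 35.
- 35 × 1.2 = 42.
- Cases: 42 / 0.14 = 300. Expected viral cases: 300 × 0.45 = 135.
- Virus-positive controls: 120 × 0.354 = 42.5.

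All stated figures reproduce. The expected bacterial count equals the required count, and the expected number of virus-positive controls exceeds it by half a child.

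**2. Chance of reaching 42 bacterial cases among 300.** Exact binomial tail, P(X ≥ 42 | 300, p). Only the 14% is in the document; the lower shares are assumptions.

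| Bacterial share | Expected cases | P(at least 42) |
|---|---|---|
| 14% (x-ray-verified CAP) | 42 | 0.53 |
| 12% (assumed) | 36 | 0.16 |
| 10% (assumed) | 30 | 0.017 |
| 7% (assumed) | 21 | <0.0001 |
| 5% (assumed) | 15 | about 0 |

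For virus-positive controls, P(X ≥ 42 | 120, 0.354) = 0.57.

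**3. Power at lower bacterial counts.** Unequal-variance normal approximation with 135 viral cases and the plan's difference and SDs: SE = √(1000²/135 + 300²/n_b), power = Φ(500/SE − 1.96).

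- n_b = 42: SE = 97.7, power 99.9%.
- n_b = 30: SE = 102.0, power 99.8%.
- n_b = 21: SE = 108.1, power 99.6%.
- n_b = 15: SE = 115.8, power 99.1%.

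With both groups divided by 1.2, to respect the plan's 20% allowance, power is still 97 to 98% at 15 bacterial cases. The large-variance group is the viral one, and it is expected to be more than three times the 42 required.

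**4. Dependence on the test.** Statistical Methods leaves the test open, subject to the number and distribution of data points. Simulation with normal data, the plan's difference and SDs, and 135 viral cases gave:

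| Bacterial cases | Mann-Whitney | Equal-variance t test |
|---|---|---|
| 42 | about 98% | about 97% |
| 21 | about 89 to 90% | about 72 to 73% |
| 15 | about 75% | about 45% |

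The equal-variance test loses power because the smaller group has the smaller SD, so pooling overstates the standard error.

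**5. Precision of specificity.** The document gives no expected specificity; about 80% is assumed. Wilson 95% intervals:

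- 34/42: 67% to 90%.
- 17/21: 60% to 92%.
- 12/15: 55% to 93%.

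**The case against.** The strongest reply has four parts.

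First, a shortfall is not proved. A reader might infer that the bacterial share must be below 14%, that 14% is an upper bound, or that 42 bacterial cases will not be delivered. The document supports none of these as fact. It gives no bacterial share for clinical CAP, the classification uses clinical, microbiological, radiographic and biochemical findings, and the figure with the algorithm is not shown, so whether the bacterial class requires an x-ray finding cannot be checked. Children without true CAP need not contribute zero bacterial classifications. This stands: the lower share is a well-grounded inference, no more.

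Second, the sample size was set for a difference in MxA levels, and that comparison survives. At the expected allocation of about 135 to 42, a count of 42 is a severe yardstick, since it is the requirement for equal groups. Even 80 viral and 15 bacterial cases would give SE = √(12,500 + 6,000) = 136 and power of about 96%. This stands for an unequal-variance test, but not for every test that the plan leaves open.

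Third, the language of certainty applies only to the cases. For virus-positive controls the text speaks of an aim and of a sufficient number. This stands. It is also true that at least 30 virus-positive controls are about 99% likely, and that 30 would give 99.8% power by the same formula.

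Fourth, no precision target for specificity is stated, so none is missed. That is true, but diagnostic accuracy is the first specific objective, and the expected precision depends directly on the bacterial count.

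None of this removes the mismatch of populations or the lack of margin.

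**Conclusion.** The point holds with moderate weight. The division is right; the input comes from a more selected population than the one enrolled, and no margin covers the difference. So 300 cases do not ensure 42 bacterial cases: the chance is 53% if 14% is exactly right, and 16%, 1.7% or below 0.01% at an assumed 12%, 10% or 7%. The 53% needs no assumption beyond the plan's own 14% and independent sampling. By the same reckoning, 120 controls give a 57% chance of at least 42 virus-positive ones, though the text claims less there.

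It would be wrong to conclude that the stated 80% power is lost. Under an unequal-variance test it is not, provided that the plan's SDs hold and about 135 viral cases accrue; that 135 rests on the 45% from the same x-ray-verified study. What is exposed is the choice of test and the precision of MxA specificity. At an assumed value of about 80%, halving the bacterial group from 42 to 21 widens the interval from 67-90% to 60-92%.

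**What to change.** Rewrite the paragraph on study size, without enrolling more:

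- State that the 14% (and the 45%) come from x-ray-verified CAP, and that 14% may be too high for WHO clinical CAP. Do not call it an upper bound.
- Give the expected number of bacterial cases over a range labelled as an assumption, for example 5% to 14%, that is 15 to 42 children among 300.
- Replace the claim that 300 cases ensure the required number with the probability of reaching 42 across that range, and give the corresponding probability for virus-positive controls.
- Restate power for the expected unequal allocation, with a test that allows unequal variances.
- Give the resulting 95% interval for MxA specificity at those counts, with the specificity used labelled as an assumption.

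The cost is one rewritten paragraph and less favourable stated figures. No further children need be enrolled.
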